##### 12.10.4.2 Discovery by potential users of the research data

The public datasets, study protocol and statistical analysis plan, will be shared through the World-Wide Antimalarial Resistance Network (WWARN) platform (<http://www.wwarn.org/working-together/sharing-data/data-available-research-community>) with a URL link provided in the data sharing section of publications, any study-specific website and WWARN's website. Our policy to data sharing, process and timelines will be provided in manuscripts and on the study website and the WWARN website. The immunological data will also be made publicly available on the IMMPORT database of NIH/NIAID. The results and anonymised data set of the FLU-PRO questionnaire will be shared with the Licence holders of FLU-PRO (NIH).

##### 12.10.4.3 Governance of access

Biological samples will be shared using material transfer agreements with the collaborating institutions (see 2.1.4 Collaborators, page 11) to minimise the risk of unauthorised analysis beyond the scope of the agreed parameters.

The full anonymized research database will be made publicly available as soon as the full study findings have been published or based on any data requests that may occur during the study or analysis is still ongoing. For the databases, we will use a controlled access approach. The data sharing policy will be provided in publications and on the respective websites. This will state that we encourage data requests. Data access will be provided to researchers after a proposal has been approved by an independent review committee identified for this purpose. An agreement on how to collaborate will be reached based on any overlap between the proposal and any ongoing efforts. Proposals can be directed to email addresses provided in the publications and websites. To gain access, data requesters will need to sign a data-sharing agreement.

The only limits to data sharing will be to safeguard research participants' confidentiality. The proposed procedures for data sharing will be set out clearly in the participant information sheet with

current and potential future risks associated with this explained to the research participants as part of the informed consent process. External users will be bound by data-sharing agreements in line with the Data Sharing Policy from the respective Sponsors and the Gates Foundation to ensure that the privacy of individuals is protected. The agreement will prohibit any attempt to (a) identify study participants from the data or otherwise breach confidentiality, (b) make unapproved contact with study participants.

## 13 TIMEFRAME AND DURATION OF THE STUDY

### 13.1 TIMELINE

The total duration of the project is projected to take 18 months, including 3 months for the preparation and approximately 12 months of patient recruitment and 3m for laboratory analysis and write up (see 13.2, Gantt chart, page 69).

### 13.2 GANTT CHART

|                                      | 2020 |    |    | 2021 |    |    |    |
|--------------------------------------|------|----|----|------|----|----|----|
|                                      | Q2   | Q3 | Q4 | Q1   | Q2 | Q3 | Q4 |
| Activity                      |      |    |    |      |    |    |    |
| Protocol development                 |      |    |    |      |    |    |    |
| IRB approval / Annual Review         |      |    |    |      |    |    |    |
| Regulatory approval/ Annual Review   |      |    |    |      |    |    |    |
| CRF and SOP development              |      |    |    |      |    |    |    |
| Drug and placebo preparation         |      |    |    |      |    |    |    |
| Drug shipment                        |      |    |    |      |    |    |    |
| Enrolment Kenya                      |      |    |    |      |    |    |    |
| Enrolment Burkina Faso               |      |    |    |      |    |    |    |
| Study                                |      |    |    |      |    |    |    |
| Closure                              |      |    |    |      |    |    |    |
| Immunological assays                 |      |    |    |      |    |    |    |
| Interim sample size re-estimation    |      |    |    |      |    |    |    |
| Observational cohort analysis        |      |    |    |      |    |    |    |
| Manuscript and results dissemination |      |    |    |      |    |    |    |

## 14 FINANCIAL ASPECTS AND CONFLICT OF INTEREST

---

### 14.1 FUNDING FOR THE TRIAL

Funding to conduct the trial is provided by the Bill and Melinda Gates Foundation. In Kenya, in-kind co-funding is provided by the US Centers for Disease Control and Prevention (CDC).

### 14.2 PROVISION OF STUDY DRUGS

Pyronaridine-artesunate will be provided free of charge by Shinpoong Pharm.co., Ltd, South Korea. Artemether-lumefantrine will be purchased. When so requested by the manufacturer, the study will provide copies of safety reports of SAEs and AEs to the manufacturers (expedited where required). The manufacturer will not be involved in the design of the trial.

### 14.3 BUDGET & BUDGET JUSTIFICATION

See section 16.8, Appendix VIII. Budget and budget justification, page 116

## 16 APPENDICES

---

### 16.1 APPENDIX I. ROLE OF INVESTIGATORS AND COLLABORATORS

#### 16.1.1 Definition investigator and collaborator

##### 16.1.1.1 Investigators

Investigators are directly engaged with the field research and live and work in Kenya and Burkina Faso, except for the trial statisticians and Chief Investigators.

##### 16.1.1.2 Collaborators

Collaborators are not directly engaged with any of the fieldwork on-site and have an advisory and supporting role either as PhD supervisors living overseas or support the study with the laboratory assays in their overseas laboratories. Each home institutions will sign MOUs in the form of MTA and/or DTAs with the overseas collaborators before samples or data can be shipped overseas.

#### 16.1.2 Protocol development: authors' contributions

The Chief Investigators wrote the first draft of the protocol. All investigators contributed to the refinement of the study protocol and approved the final versions.

## 16.2 APPENDIX II. TERMS OF REFERENCE STUDY MANAGEMENT GROUP AND DSMB

The study will have the following committees and governance structure. All committees will act in accordance with the International Clinical Harmonization Guidelines for Good Clinical Practice (GCP) Principles.

## 16.2.1 Study Management Group (TMG)

### 16.2.1.1 Membership

The Chief Investigators (2x, ad hoc) and Country Co-Principal Investigators (4x) or representatives, the country study coordinator(s), lead data manager, lead administrators. Others involved in the day to day running of the trial are invited ad hoc.

### 16.2.1.2 Responsibilities

The TMG is responsible for the administrative management and day to day running of the study. Their activities will include study planning, organising TMG and DSMB meetings, providing reports to the DSMB, regulators, and ethics committees, SUSAR [Serious unexpected suspected adverse events] reporting, maintaining the study/trial master file, budget administration and contractual issues, the organisation of central data management and sample collection. The TMG will also monitor the conduct of the study by reviewing monthly reports prepared by the data managers and statisticians of accrual and baseline characteristics, data completeness, specimen collection, and adverse events (AEs). The study team will also review individual participant-level safety data frequently to assess the relation of all reported AEs to study treatment.

## 16.2.2 Data Safety and Monitoring Board (DSMB)

### 16.2.3 Membership

An independent data and safety monitoring board (DSMB) will be convened for this study. The DSMB will consist of four independent members with expertise in coronavirus disease (COVID-19) or respiratory viruses, antiviral therapies and shedding, malaria, and a biostatistician. If so required, in addition to the core members, a topic expert can be invited by the chair of the DSMB on an ad hoc basis to attend. An unblinded biostatistician may also be invited to attend part of the closed sessions to present the most current data from the trial or provide the allocation code for certain participants.

#### 16.2.3.1 Operational

The DSMB meetings will be conducted via teleconference and consist of an open session, followed by a closed session. The open sessions can be attended by representatives of the investigators, including the Chief Investigators, Country Principal Investigators, and study statistician. Other investigators can also attend open session on an ad hoc basis. The funder can attend open DSMB sessions as observers. The Chair and at least one of the three other independent members together will constitute a quorum.

The DSMB will have a start-up meeting to discuss its mandate and discuss the protocol. If possible, a second meeting will take place shortly after the commencement of the study, e.g. when approximately 10% of participants have been recruited. After that, the frequency of the meetings will be determined by the Chair of the DSMB in consultation with the Chief Investigators. It is anticipated that the DSMB will generally meet twice per year during the life span of the study and have one meeting at the closure of the study.

During the first meeting, the DSMB members will review the timeline set out in the protocol for participant recruitment, informed consent documents and plans for data safety monitoring. Prior to subsequent meetings, open reports containing accrual and retention rates, participant characteristics, and serious adverse events will be sent to the DSMB members the week prior to any DSMB meeting. Only the DSMB members and the unblinded biostatistician will receive password-

protected closed reports of SARS-CoV-2 endpoints by randomisation arm. A full confidential report should be submitted in writing to the Chief Investigator at the end of each DSMB meeting

#### **16.2.3.2 Role of the DSMB**

They are independent and look at the study overall and the nested malaria treatment trial from an ethical point of view of the participant safety, future participants, and society in general. It is their responsibility to prevent participants from being exposed to any excess risks by making a recommendation to the Investigators for the study or trial suspension or early termination if the safety or efficacy results are sufficiently convincing. For the nested trial component, the DSMB can choose whether to review the data blinded or to see unblinded data and analyses by study arm. A DSMB charter will be developed for this study that will supersede this section of the protocol. Any changes in the role of the DSMB relative to this protocol text will not be considered a protocol deviation and does require an amendment. Briefly, some of the suggested roles of the DSMB will include:

- To evaluate the progress of the study/trial in relation to the timeliness, data quality and other factors that can affect the overall objectives of the trial
- To ensure participant rights and safety are adhered to and that the protocol demands freely given informed consent
- To conduct any interim reviews if specified) when adequate data have been accrued of blinded or unblinded safety data and report back to the Chief Investigators with a recommendation whether the study or nested trial should continue, the protocol be modified, or the trial or trial arm be stopped.
- Review and any major deviations from the study protocol
- To review relevant information from other sources
- To review and approve modifications to the overall enrolment target based on the event rate.
- To inform the Chief Investigators and TMG of the need to make changes to the trial protocol
- To consider the blinded or unblinded interim data from the study and nested trial and relevant information from other sources.
- To determine how frequently any interim analysis of study or trial data should be undertaken.
- To consider any requests for unblinding and release of interim trial data and to recommend on the importance of this.
- To ensure that the study results are disseminated appropriately, and consideration be given to the implementation of the results into policy

### 16.3 APPENDIX III. DECLARATION OF HELSINKI

#### WORLD MEDICAL ASSOCIATION DECLARATION OF HELSINKI

Recommendations guiding physicians in biomedical research involving human subjects. Adopted by the 18th World Medical Assembly, Helsinki, Finland, June 1964. Amended by the 29th World Medical Assembly, Tokyo, Japan, October 1975, 35th World Medical Assembly, Venice, Italy, October 1983, 41st World Medical Assembly Hong Kong, September 1989 and the 48th General Assembly, Somerset West, Republic of South Africa, October 1996

#### INTRODUCTION

It is the mission of the physician to safeguard the health of the people. His or her knowledge and conscience are dedicated to the fulfilment of this mission.

The Declaration of Geneva of the World Medical Association binds the physician with the words, "The health of my patient will be my first consideration", and the International Code of Medical Ethics declares that, "A physician shall act only in the patient's interest when providing medical care which might have the effect of weakening the physical and mental condition of the patient."

The purpose of biomedical research involving human subjects must be to improve diagnostic, therapeutic and prophylactic procedures and the understanding of the aetiology and pathogenesis of disease.

In current medical practice, most diagnostic, therapeutic or prophylactic procedures involve hazards. This applies especially to biomedical research.

Medical progress is based on research which ultimately must rest in part on experimentation involving human subjects.

In the field of biomedical research, a fundamental distinction must be recognized between medical research in which the aim is essentially diagnostic or therapeutic for a patient, and medical research, the essential object of which is purely scientific and without implying direct diagnostic or therapeutic value to the person subjected to the research.

Special caution must be exercised in the conduct of research which may affect the environment, and the welfare of animals used for research must be respected.

Because it is essential that the results of laboratory experiments be applied to human beings to further scientific knowledge and to help suffering humanity, the World Medical Association has prepared the following recommendations as a guide to every physician in biomedical research involving human subjects. They should be kept under review in the future. It must be stressed that the standards as drafted are only a guide to physicians all over the world. Physicians are not relieved from criminal, civil and ethical responsibilities under the laws of their own countries.

#### Basic principles

- Biomedical research involving human subjects must conform to generally accepted scientific principles and should be based on adequately performed laboratory and animal experimentation and on a thorough knowledge of the scientific literature.
- The design and performance of each experimental procedure involving human subjects should be clearly formulated in an experimental protocol which should be transmitted for consideration, comment and guidance to a specially appointed committee independent of the investigator and

the sponsor provided that this independent committee is in conformity with the laws and regulations of the country in which the research experiment is performed.

- Biomedical research involving human subjects should be conducted only by scientifically qualified persons and under the supervision of a clinically competent medical person. The responsibility for the human subject must always rest with a medically qualified person and never rest on the subject of the research, even though the subject has given his or her consent.
- Biomedical research involving human subjects cannot legitimately be carried out unless the importance of the objective is in proportion to the inherent risk to the subject.
- Every biomedical research project involving human subjects should be preceded with careful assessment of predictable risks in comparison with foreseeable benefits to the subject or to others. Concern for the interests of the subject must always prevail over the interests of science and society.
- The right of the research subject to safeguard his or her integrity must always be respected. Every precaution should be taken to respect the privacy of the subject and to minimize the impact of the study on the subject's physical and mental integrity and on the personality of the subject.
- Physicians should abstain from engaging in research projects involving human subjects unless they are satisfied that the hazards involved are believed to be predictable. Physicians should cease any investigation if the hazards are found to outweigh the potential benefits.
- In publication of the results of his or her research, the physician is obliged to preserve the accuracy of the results. Reports of experimentation not in accordance with the principles laid down in this Declaration should not be accepted for publication.
- In any research on human beings, each potential subject must be adequately informed of the aims, methods, anticipated benefits and potential hazards of the study and the discomfort it may entail. He or she should be informed that he or she is at liberty to abstain from participation in the study and that he or she is free to withdraw his or her consent to participation at any time. The physician should then obtain the subject's freely-given informed consent, preferably in writing.
- When obtaining informed consent for the research project, the physician should be particularly cautious if the subject is in a dependent relationship to him or her or may consent under duress. In that case the informed consent should be obtained by a physician who is not engaged in the investigation and who is completely independent of this official relationship.
- In case of legal incompetence, informed consent should be obtained from the legal guardian in accordance with national legislation. Where physical or mental incapacity makes it impossible to obtain informed consent, or when the subject is a minor, permission from the responsible relative replaces that of the subject in accordance with national legislation. Whenever the minor child is in fact able to give a consent, the minor's consent must be obtained in addition to the consent of the minor's legal guardian.
- The research protocol should always contain a statement of the ethical considerations involved and should indicate that the principles enunciated in the present Declaration are complied with.

#### Medical research combined with professional care (Clinical Research)

- In the treatment of the sick person, the physician must be free to use a new diagnostic and therapeutic measure, if in his or her judgement it offers hope of saving life, re-establishing health or alleviating suffering.
- The potential benefits, hazards and discomfort of a new method should be weighed against the advantages of the best current diagnostic and therapeutic methods.

- In any medical study, every patient - including those of a control group, if any - should be assured of the best proven diagnostic and therapeutic method. This does not exclude the use of inert placebo in studies where no proven diagnostic or therapeutic method exists.
- The refusal of the patient to participate in a study must never interfere with the physician-patient relationship.
- If the physician considers it essential not to obtain informed consent, the specific reasons for this proposal should be stated in the experimental protocol for transmission to the independent committee (1,2).
- The physician can combine medical research with professional care, the objective being the acquisition of new medical knowledge, only to the extent that medical research is justified by its potential diagnostic or therapeutic value for the patient.

Non-therapeutic biomedical research involving human subjects (Non-clinical biomedical research)

- In the purely scientific application of medical research carried out on a human being, it is the duty of the physician to remain the protector of the life and health of that person on whom biomedical research is being carried out.
- The subjects should be volunteers -- either healthy persons or patients for whom the experimental design is not related to the patient's illness.
- The investigator or the investigating team should discontinue the research if in his/her or their judgement it may, if continued, be harmful to the individual.
- In research on man, the interest of science and society should never take precedence over considerations related to the well-being of the subject.

## 16.4 APPENDIX IV. WHO clinical progression scale

Figure 6: WHO clinical progression scale

| Patient State                  | Descriptor                                                                             | Score |
|--------------------------------|----------------------------------------------------------------------------------------|-------|
| Uninfected                     | Uninfected; no viral RNA detected                                                      | 0     |
| Ambulatory mild disease        | Asymptomatic; viral RNA detected                                                       | 1     |
|                                | Symptomatic; independent                                                               | 2     |
|                                | Symptomatic; assistance needed                                                         | 3     |
| Hospitalised: moderate disease | Hospitalised; no oxygen therapy*                                                       | 4     |
|                                | Hospitalised; oxygen by mask or nasal prongs                                           | 5     |
| Hospitalised: severe diseases  | Hospitalised; oxygen by NIV or high flow                                               | 6     |
|                                | Intubation and mechanical ventilation, $pO_2/FiO_2 \geq 150$ or $SpO_2/FiO_2 \geq 200$ | 7     |
|                                | Mechanical ventilation $pO_2/FiO_2 < 150$ ( $SpO_2/FiO_2 < 200$ ) or vasopressors      | 8     |
|                                | Mechanical ventilation $pO_2/FiO_2 < 150$ and vasopressors, dialysis, or ECMO          | 9     |
| Dead                           | Dead                                                                                   | 10    |

ECMO=extracorporeal membrane oxygenation.  $FiO_2$ =fraction of inspired oxygen. NIV=non-invasive ventilation.  $pO_2$ =partial pressure of oxygen.  $SpO_2$ =oxygen saturation. \*If hospitalised for isolation only, record status as for ambulatory patient.

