|                                                                                                                                                                                                                                                                                      |                                                                                                                                                                                                                                                                                                                                                                                                                        |
|--------------------------------------------------------------------------------------------------------------------------------------------------------------------------------------------------------------------------------------------------------------------------------------|------------------------------------------------------------------------------------------------------------------------------------------------------------------------------------------------------------------------------------------------------------------------------------------------------------------------------------------------------------------------------------------------------------------------|
|                                                                                                                                                                                                                                                                                      | 
 
Time to clearance of nasal SARS-CoV-2, defined as negative SARS-CoV-2 RNA PCR tests (swabs collected on days 1, 3, 7, 14, 21 and 28)
 
                                                                                                                                                                                                                                 |

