- a Screening for Covid-19 as part of a screening study (cross-sectional survey, source population). Screening and Day 1 evaluations may occur on the same day if the point of care antigen SARS-CoV-2 tests result is positive. This depends on the malaria status of the patient (i.e. malaria positive: Invite eligible participants to enrol in the nested malaria treatment trial on Day-0; malaria-negative: Provide the participant with the option to enrol in the COVID-19 cohort study either the same day (Day-0) or wait until the confirmatory PCR results are available on Day-1 (see e, below)). A sub-group of participants who test negative by both SARS-CoV-2 antigen RDT and malaria RDT, and are feeling well, will be invited to participate as healthy controls.
- b These evaluations will be conducted by telephone and/or text messaging
- c These evaluations will be conducted among participant enrolled in the nested malaria treatment trial only
- d Any default diagnostic swab performed by local health authorities is acceptable. Additional swabs will be taken for a SARS-CoV-2 point of care antigen test.
- e The number of days for the SARS-CoV-2 test results to become available can be longer than 1 day and may vary by site.
- f Blood sample for SARS-CoV-2, malaria diagnostics and malaria and non-malaria serology in source population (fingerpick, 250 µL dried blood spot and malaria RDT). Consenting healthy control participants will provide a single 5 mL venous blood sample for CyTOF for B and T cell markers (fixed whole blood), Olink immunoassay (plasma) and transcriptional profiling (gene expression).
- g Saliva sample (~1mL) for SARS-CoV-2 RNA and antigen detection and SARS-CoV-2 and malaria serology
- h Includes questions for the WHO Ordinal Scale for Clinical Improvement and/or modified Flu-PRO PLUS
- i Daily during the first 14 days, or until the participant is asymptomatic for two consecutive days, whichever comes last, and then on days 21, 28 and 42
- j Mid-nasal swabs for research specific molecular detection and viral load and sequencing of SARS-CoV-2 (for later batch analysis, not for patient care)

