## 10.3 ASSESSMENT OF CLINICAL AND EPIDEMIOLOGICAL ENDPOINTS

### 10.3.1 Assessment of disease progression

Disease severity, will be compared between the groups daily over the first 14 days and then at days 21 and 28. We will use the updated WHO Clinical Progression Scale (see 16.4, Appendix IV. WHO clinical progression scale, page 82).

Alternately, we will consider the inFLUenza Patient-Reported Outcome instrument (Flu PRO) PLUS – Modified for SARS-CoV-2. FLU-PRO is a well-established instrument for the collection of respiratory symptoms (see 16.5, Appendix V. Modified Flu-PRO PLUS scale, page 83).

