### 11.2.4.2 Continuous endpoints

Continuous endpoints will be summarised using the number of subjects (n), mean, standard deviation (SD), geometric mean (95% CI), minimum, median (50th percentile), 25th and 75th percentiles and maximum by treatment group. For continuous endpoints with single measurements, a GLM model with a normal distribution and identity link function will be used, with the stratification factors 'site' and 'presence of symptoms' as covariates in the crude models and with additional co-

variates in adjusted models. Results will be expressed as the mean differences with their two-sided 95% CIs will be derived from the GLM model. For continuous endpoints with repeated measurements, a GLMMIX with the identity function and normal distribution will be used.

Non-normally distributed data will be transformed to obtain an approximately normal distribution. For example, antibody titres to COVID-19 will be summarised by geometric mean (the Geometric Mean Titre or GMT) (95% CI) by group, and groups compared using the Geometric Mean (Titre) Ratio (GMTR, or GMR) and associated 95% CIs (see also 11.2.4.4, Immunological responses, below).

If variables do not attain a normal distribution after transformation, results will be expressed and the median and 25% and 75% percentile by group and compared using the Wilcoxon rank-sum test.

For the analysis of the disease progression and clinical scales including the WHO clinical progression scale and the FLU-PRO scales, we will use change scores (95% CI) defined as the mean difference between the score at enrolment and the score by defined timepoints, or the maximum score achieved.

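### WHO scores 0 and 1 differ only by viral RNA, so the secondary change-score analysis of severity counts viral clearance in a symptom-free participant as a one-point improvement

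*Protocol*

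**What the plan says.** Protocol 16.4 (Appendix IV) gives score 0 as "Uninfected; no viral RNA detected", score 1 as "Asymptomatic; viral RNA detected" and score 2 as "Symptomatic; independent". From score 2 upwards the levels depend on symptoms, hospital care, organ support or death, with no RNA criterion. Participants admitted for isolation only are scored as ambulatory.

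Protocol 10.3.1 says "Disease severity, will be compared between the groups daily over the first 14 days and then at days 21 and 28". For the instrument, the same section states: "We will use the updated WHO Clinical Progression Scale". It names FLU-PRO PLUS as an alternative.

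Protocol 11.2.4.2 says of the clinical scales that "we will use change scores (95% CI) defined as the mean difference between the score at enrolment and the score by defined timepoints". It also allows each participant's highest score to be analysed instead.

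The endpoint tables in 2.2.3 and 4 list "swabs collected on days 1, 3, 7, 14, 21 and 28". In the schedule of activities (2.2.4), footnote c restricts the day-21 swab to nested-trial participants, and footnote b makes the days between visits telephone or text contacts. Research swabs are "for later batch analysis, not for patient care" (footnote j). The protocol prints no rule for choosing between 0 and 1 when there is no RNA result.

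**The concern.** Viral shedding and COVID-19 severity are separate objectives in section 4, for both the cohort and the nested trial. The change score mixes them. A symptom-free participant who turns RNA-negative moves from 1 to 0, and the analysis treats that move as equal to any other one-point step on the scale.

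Two consequences follow:

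- A difference between groups in clearance alone appears as a difference in severity, although no participant is clinically better.
- Without a swab, a symptom-free participant has no determinable score. The availability of swabs is also unequal: at day 21 only nested-trial participants, who are malaria-positive, can be scored 0, and 10.3.1 compares severity by malaria status on that day.

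The stratum concerned is not small. Section 7.3 says at least half of the cases identified in Kenya are asymptomatic. No corresponding figure is given for Burkina Faso.

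**Working it through.** **1. The protocol's own figures.** Cohort (11.1.1): 30% vs 45%, 538 and 135 completers, two-sided α 0.05.
- Pooled proportion = (538×0.30 + 135×0.45)/673 = 0.330.
- SE under no difference = √[0.330×0.670×(1/538 + 1/135)] = 0.0453.
- SE under the alternative = √(0.21/538 + 0.2475/135) = 0.0472.
- Power = Φ[(0.15 − 1.96×0.0453)/0.0472] = Φ(1.30) = 0.903. Stated: 90%.

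Nested trial (11.1.3): 20% vs 42.2% with 67 per arm gives power 0.800. Stated: 80%.

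Both reproduce, and neither depends on the 0/1 step. The cohort endpoint starts from asymptomatic or mild disease taken together, and the nested-trial endpoint is clearance itself.

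**2. Comparison days without a swab.** Days 1 to 14 plus days 21 and 28 make 16 comparison times.
- Malaria-negative: swabs on days 1, 3, 7, 14 and 28, so 16 − 5 = 11 without a swab.
- Malaria-positive in the nested trial: also day 21, so 16 − 6 = 10 without a swab.

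This follows footnote c of the schedule. If the endpoint-table list applied to the whole cohort, both counts would be 10 and the day-21 imbalance would vanish.

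**3. Size of the spurious shift at day 7.**
- From the protocol: clearance 20% vs 42.2%, and 67 per arm.
- Assumed: 50% asymptomatic (score 1) and 50% at score 2 at enrolment; half of the symptomatic are symptom-free by day 7; clearance is independent of symptoms; an equal share *q* in each arm is at score 4 on day 7; no clinical difference between arms.

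Symptom-free share among those not progressed = 0.5 + 0.5×0.5 = 0.75.

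Shift = (1 − *q*) × 0.75 × (0.422 − 0.20) = 0.1665 × (1 − *q*).

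For *q* = 0, the change has this distribution:
- AL: −2 with probability 0.05, −1 with 0.30, 0 with 0.65; mean −0.400, variance 0.500 − 0.160 = 0.340.
- PA: −2 with probability 0.1055, −1 with 0.3555, 0 otherwise; mean −0.5665, variance 0.7775 − 0.3209 = 0.457.
- SE = √[(0.340 + 0.457)/67] = 0.109; ratio 0.1665/0.109 = 1.53; rejection probability Φ(1.53 − 1.96) ≈ 33%.

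For *q* > 0 the calculation is the same, with moves of +3 (from score 1) and +2 (from score 2) added in both arms:

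| Share at score 4, day 7 (assumed) | Shift (points) | SE | Rejection |
|---|---|---|---|
| 0% | 0.167 | 0.109 | about 33% |
| 10% | 0.150 | 0.188 | about 13% |
| 22.5% | 0.129 | 0.239 | about 8% |
| 30% | 0.117 | 0.258 | 7–8% |
| 45% | 0.092 | 0.275 | about 6% |

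Simulated t-tests agree with these figures to within about one percentage point. With scores 0 and 1 merged, the shift is 0 and rejection returns to about 5% in every row.

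**4. Day 21 in the cohort.** Suppose symptom-free malaria-negative participants are carried at 1 because they have no swab. The artefact is then −(asymptomatic share × cleared share). At an assumed 50% × 50% it is −0.25 points in favour of the malaria-positive group. With each share between 25% and 75% it runs from −0.06 to −0.56.

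**The case against.** The strongest reply concerns size. Section 11.1.1 assumes that 30% to 45% of the cohort progress by day 28. For someone asymptomatic or mild at enrolment that means reaching at least score 4, a move of up to three points from scores 1 and 2. A reader might infer that the RNA step dominates the score, or that a third of null trials would show a false severity effect. The protocol supports neither. The 33% needs nobody to have worsened, and the rate falls towards 5% once some participants sit at score 4. The mean shift remains.

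A reader might also infer that nobody can be scored on a day without a swab. Only symptom-free participants are affected, because scores 2 to 10 need no RNA result. The schedule (footnote h) attaches the WHO-scale questions to clinic-visit days, and the daily pattern is also that of FLU-PRO, which uses no RNA. If the comparison were confined to swab days, the missing-score problem would largely disappear. The one-point credit for clearance would not, and 10.3.1 as written names the WHO scale for the daily comparison. Later batch testing is no obstacle, because each result belongs to a dated swab.

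The nested trial's severity endpoint is a severity index score that section 4.3 does not identify as the WHO scale. It stands beside the proportions of days with fever and with respiratory symptoms, which do not involve RNA. This point stands, and it limits how far the problem reaches the nested trial.

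Finally, a scoring convention could be left to the SAP. But the protocol already fixes the scale, the comparison days and the mean change score, and together these produce the bias.

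**Conclusion.** The point holds for the secondary change-score analyses of the WHO scale. Followed as written, they credit viral clearance in symptom-free participants as reduced severity. They also leave those participants without a determinable score on 10 or 11 of 16 comparison days, and day-21 scoring differs by exposure group under the schedule's footnote c.

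The illustrative bias is about 0.09 to 0.17 points at day 7. It rests on the protocol's clearance rates and on assumed values for the asymptomatic share, recovery and progression. The false-positive rate depends heavily on how many participants have worsened, from about 33% down to about 6%.

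It would be wrong to conclude that the primary results are compromised. The cohort's binary progression endpoint does not use the 0/1 step and its power reproduces. The nested-trial primary endpoint is clearance itself. The maximum score is essentially unaffected because participants enter with confirmed infection. The nested trial's severity analysis is touched only so far as its severity index score is the WHO scale.

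**What to change.** State in 10.3.1 and 11.2.4.2 that severity change-score analyses of the WHO scale merge scores 0 and 1 into one level (no symptoms, irrespective of RNA), and that RNA status is analysed only under the viral endpoints. This removes the spurious shift. It also lets a symptom-free participant be scored on any day with a symptom report, in both exposure groups. The same edit should say whether the nested trial's severity index score is the WHO scale.

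No new data or visits are needed. The cost is that these analyses depart from the published 0–10 coding. That coding can still be reported descriptively on the swab days common to both groups (1, 3, 7, 14 and 28).
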